### Data collection methods

Baseline demographic data will be collected by way of pre-intervention questionnaires. Participants will also answer a 5-point Likert-scale question about intention to be screened with PSA test.

Upon receiving the decision aid and, when applicable, values clarification method reading/completion, participants will answer the post-intervention questionnaire, containing the Portuguese validated translation of the DCS, as well as the same above mentioned Likert-scale question about intention to undergo PSA screening.

### Data management

Participant paper files, only identifiable by a participant ID number, will be stored in numerical order in a secure place at the University of Porto. Participant paper files will be maintained in storage for a period of 3 years after completion of the study. All anonymized data will be entered electronically and, only after all data has been entered, will researchers contact the statistician who prepared the randomization schedule to know which group was assigned to individual participants access to the study data will be restricted to the research team based at University of Porto. A data tracking system with time stamps will be implemented for audit purposes. A password system will be utilized to control access to de-identified electronic data and these passwords will be changed every 3 months.

To ensure that we can follow participants for screening participation after 12 months, we will keep a single file which links participant ID number to participant name, phone number and one next of kin phone number. This electronic file will be kept by a team researcher not based at the University of Porto.

Anonymized data will be analyzed on a personal computer belonging to one of the authors based at the University of Porto.

### Statistical methods

After collection, data will be analyzed using Microsoft Excel 2016® and SPSS Statistics 25.0®. Participants will be analyzed in the group they were randomized to, regardless of actual intervention received. In order to analyze between group differences concerning perceived clarity of personal values, we will use One-way ANOVA (if the variable distribution is normal) or Kruskal-Wallis (if the variables are not distributed normally). Normal distribution of variables will be assessed by observing the respective histograms and validated with the Kolmogorov-Smirnov test. For continuous variables with normal distributions, data will be described using mean (M), standard deviation (SD), minimum (min), and maximum (max). For continuous variables not distributed normally, data will be described using median (Med) and the respective interquartile range [Q_1_; Q_3_]; Q_1_ being the first quartile and Q_3_ being the third quartile.

If either the ANOVA or Kruskal-Wallis tests demonstrates significant differences between groups, multiple comparisons will be conducted between groups pairs in order to detect between which groups there are differences.

To test independence between categorical variables, we will use Chi-square test for independence. Categorical variables will be described using absolute and relative frequencies, N (%). *p*-values ≤0.05 will be considered significant.

DCS total score is composed of 16 items (each one with a 5-point Likert response scale) divided in five subscores: uncertainty subscore (3 items), informed subscore (3 items), values clarity subscore (3 items), support subscore (3 items), effective decision subscore (4 items). For each participant partial scores and a total score will be calculated. Concerning missing values, those participants who do not answer at least 50% of the items of each subscale will be excluded from the analysis. The total score will be presented on a 0–100 scale [23].

If there are baseline differences between groups, we will perform multivariate analysis using linear multiple regression.

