**Methods:**

Male factory employees from an industrial facility in the Northern region of Portugal aged 50 to 69 years old will be randomly assigned to one of three decision aid groups used to support prostate cancer screening decisions: (i) decision aid with information only (control), (ii) decision aid with information plus an implicit VCM, (iii) decision aid with information plus an explicit VCM.

Men will be allowed release time from work to attend a session at their workplace. After a brief oral presentation, those willing to participate in the study will fill the baseline questionnaire, plus a 5 point-Likert scale question about intentions to undergo screening, and will then receive the intervention materials to complete.

We estimated a total sample size of 276 participants; with 92 in each group.

The primary outcome will be the perceived clarity of personal values assessed by the Portuguese validated translation of the three subscales of the Decisional Conflict Scale. Secondary outcomes will be intention to be screened (before and after the intervention), the total score from the Decisional Conflict Scale and the self-report of having or not undergone screening at 6 months.

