### Outcomes

The primary outcome will be the perceived clarity of personal values assessed by the Portuguese validated translation of the three subscales of the Decisional Conflict Scale (DCS) [22]. The Values Clarity subscores range from 0 (feels extremely clear about personal values for benefits and risks/side effects) to 100 (feels extremely unclear about personal values); lower scores suggest better clarity.

Secondary outcomes will be intention to be screened and the total score from DCS. Respondents will be asked a single question about their intention to undergo a PSA screening, using a 5 point-Likert scale (ranging from “strongly disagree” to “strongly agree”; intention to undergo PSA screening will be considered positive if the respondent replies with “agree” or “strongly agree”). Total scores from the 16-questions DCS (including the subscales values clarity, informed decision making, effective decision making, decision making support, decision making uncertainty) range from 0 (no decisional conflict) to 100 (extremely high decisional conflict), discriminating between those who make and delay decisions [23]. Furthermore, prostate cancer screening status at 6 months after the intervention will be assessed by way of a self-report.

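### Screening intention: the dichotomy with a chi-square test is valid between arms but inefficient, since it makes no routine use of the baseline answer and drops most of the five-point scale

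*Protocol article*

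**What the plan says.** All references are to the protocol article.

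- **Outcome.** The abstract's Methods paragraph lists as a secondary outcome "intention to be screened (before and after the intervention".
- **Instrument.** Under Outcomes: "Respondents will be asked a single question about their intention to undergo a PSA screening, using a 5 point-Likert scale". Data collection methods has it answered before the intervention ("Participants will also answer a 5-point Likert-scale question about intention to be screened with PSA test") and again in the post-intervention questionnaire ("as well as the same above mentioned Likert-scale question about intention to undergo PSA screening").
- **Dichotomy.** Under Outcomes, "intention to undergo PSA screening will be considered positive if the respondent replies with" agree or strongly agree. The other three answers count as not positive.
- **Test.** Statistical methods ties one-way ANOVA or Kruskal-Wallis to perceived clarity of values. For categorical data it gives one method: "To test independence between categorical variables, we will use Chi-square test for independence".
- **Adjustment.** The same section closes with "If there are baseline differences between groups, we will perform multivariate analysis using linear multiple regression". It names no covariate and no outcome.

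**The concern.** Two pieces of information are collected and then not used by default.

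The first is the baseline answer. It is the same item, answered by the same man in the same session, so it can be expected to predict the later answer well. A between-arm test on the later answer alone leaves that explained variation in the error. The regression clause does not reliably close the gap. It depends on observed imbalance, whereas the gain in precision from a prognostic baseline exists whether or not the arms happen to differ. A linear model is also not the natural one for a yes/no outcome.

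The second is the scale. With the cut between neutral and agree, a move from strongly disagree to neutral, or from agree to strongly agree, counts as no movement.

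At stake is the power to see whether the values clarification methods shift intention. The sample size was set on the primary outcome, so no margin was planned for this one.

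**Working it through.** **1. The plan's own figure.** The Sample size section gives 276 men (92 per arm) for a three-group ANOVA with effect size 0.2, alpha 0.05, 80% power and 10% loss. Reading 0.2 as Cohen's f, the noncentral F calculation gives a smallest balanced total of 246 (82 per arm, power 0.804). Then 82/0.9 = 91.1, rounded up to 92, and 3 × 92 = 276. The figure reproduces. It concerns the primary outcome; no power is stated for intention.

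**2. Assumptions for intention (none is in the document).**
- A latent normal intention is cut into five levels, with 58% positive at baseline.
- Latent arm shifts are -0.2, 0 and +0.2 SD, equivalent to f = 0.2 × √(2/3) = 0.163.
- There are 82 men per arm.
- The latent pre-post correlation is 0.3, 0.5 or 0.7.

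**3. Chi-square on the dichotomy, in closed form.** The cut is at Φ⁻¹(0.42) = -0.202.
- Proportions positive after the intervention: Φ(0.202 - 0.2) = 0.501, 0.580 and Φ(0.202 + 0.2) = 0.656; mean 0.579.
- Noncentrality = 82 × Σ(p - 0.579)² / (0.579 × 0.421) = 4.06.
- With 2 degrees of freedom and critical value 5.99, power is 0.42. Simulation gives 42-43%.

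**4. Alternatives under the same assumptions (simulation).**

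| Analysis of the post-intervention answer | r = 0.3 | r = 0.5 | r = 0.7 |
|---|---|---|---|
| Chi-square on the dichotomy | 42-43% | 42-43% | 42-43% |
| Five levels, linear score, adjusted for baseline | 57% | 67% | 79% |
| Five levels, proportional odds, adjusted for baseline (400 runs per setting) | 62% | 66% | 81% |

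An unadjusted five-level Kruskal-Wallis test has 56-58%. Type I error was near 5% for the chi-square, Kruskal-Wallis and linear-score analyses, and 3-4% for the proportional-odds model in its smaller simulation. At a correlation of 0.3 most of the gain therefore comes from keeping the five levels; at 0.5 and above the baseline answer adds clearly more.

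**5. Sensitivity to the assumptions.** With a larger effect (f = 0.2) and 60% or 80% positive at baseline, the powers are:
- chi-square: 47-60%;
- Kruskal-Wallis: 69-77%;
- baseline-adjusted linear score: 79-84% at r = 0.5 and 90-94% at r = 0.7.

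The levels move, but the ordering does not.

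**6. Only if within-group change is tested.** This simulation used 246 men, 60% positive, no true change, correlations of 0.5-0.8 and a nominal 5% level.
- Chi-square treating the two occasions as separate samples: rejects in 0.4-1.8% of runs.
- McNemar: rejects in 4.3-4.8%.
- Independence test on the before-by-after table: rejects in 99.9-100%, because it tests association and not change.

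**The case against.** **The link to the chi-square is inferred.** Statistical methods does not name intention beside the test. That is so, but Outcomes makes intention binary and no other categorical method is offered, so this is the natural reading.

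**The planned comparison is not wrong.** This stands. After randomisation, a chi-square on post-intervention proportions keeps its type I error, and the cut-point is fixed in advance and gives a readable result. The charge is lost information only.

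**Invalid use on paired answers.** A reader might infer, from an outcome described as before and after and a single independence test, that the plan applies that test to paired answers and so gets wrong standard errors. The document does not support this. It nowhere assigns the chi-square to a before-after comparison, and not naming a paired method in a condensed article is no error. Step 6 of the working is therefore only a conditional warning.

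**Adjustment is provided for.** The regression clause could take in baseline intention, so it would be too strong to call the plan unadjusted without qualification. What remains is that the clause is conditional, linear and not tied to this covariate.

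**The power figures are assumed, and 82 per arm may be too few.** Both answers are given in one session, so losses should be small. At 92 per arm the noncentrality is 4.06 × 92/82 = 4.56 and chi-square power is about 47%. The alternatives would gain too.

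**Conclusion.** The point holds as one of efficiency on a secondary outcome. By default the plan compares a dichotomised answer between arms, with no routine use of a baseline value it has already collected. Under the stated assumptions the loss against a baseline-adjusted five-level analysis runs from about 14 points (57 - 43) at a correlation of 0.3 to about 37 points (79 - 42) at 0.7. The direction held under both sets of assumptions tried. The absolute levels depend on response distribution, effect and correlation, none of which the protocol gives. The between-arm test is valid, and the primary outcome and the total of 276 are untouched.

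**What to change.** In Statistical methods, add a sentence for screening intention:

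- Compare post-intervention intention between arms on its five levels, with arm and baseline intention as covariates, whatever the observed balance. Use a proportional-odds model, with a linear-score ANCOVA named in advance as the fallback if that assumption fails. Report estimates with 95% confidence intervals.
- Keep the proportion positive, as defined under Outcomes, as a supportive result from a logistic regression adjusted for baseline intention.
- If within-group change is tested, use McNemar (dichotomy) or Wilcoxon signed-rank (five levels), not the independence test.

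The cost is wording only: no extra men, visits or questions. Odds ratios are less familiar than percentages, so the percentages should still be shown, and the proportional-odds assumption has to be checked.

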### Sample size

We estimated a total sample size of 276 participants, 92 in each group, using the ANOVA test for three groups and considering an average effect size of 0.2 with a significance level of 0.05 and 80% power, attending to the psychometric properties of the DCS and also accounting for 10% of participants leaving the study before conclusion.

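### As worded, the DCS missing-item rule can drop a man with a complete values-clarity score from the primary analysis because of blanks on other subscales; the 50% rule should be applied score by score.

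*Protocol article*

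**What the plan says.** The Outcomes section states: "The primary outcome will be the perceived clarity of personal values". It describes the Values Clarity subscore, on a 0–100 scale, as its measure. (The sentence naming the instrument mentions three DCS subscales, but only this one is described. I take the 3-item Values Clarity subscore as the primary outcome.) The total is secondary: "Secondary outcomes will be intention to be screened and the total score from DCS".

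Statistical methods lists five subscores over 16 items: uncertainty and informed, with 3 items each, then "values clarity subscore (3 items), support subscore (3 items), effective decision subscore (4 items". After saying that partial and total scores will be calculated for each participant, it sets the missing-item rule: "those participants who do not answer at least 50% of the items of each subscale will be excluded from the analysis". No other text limits or explains the rule.

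The DCS is completed after allocation and after the decision aid has been read. Data collection methods says "participants will answer the post-intervention questionnaire, containing the Portuguese validated translation of the DCS".

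**The concern.** The primary outcome needs 3 of the 16 items. Only the total score, a secondary outcome, draws on all five subscales. The rule nevertheless makes a man's place in the analysis depend on every subscale being at least half answered. The other 13 items can therefore remove him when his primary outcome is fully observed.

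Two things are at stake. First, observed primary data on randomised men are discarded, for no purpose that the protocol states. Second, the exclusion depends on behaviour after the intervention, so it could disturb the comparison if skipping differed between arms. The protocol gives no evidence that it would.

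There is also a reproducibility problem. Two analysts could read the sentence differently and build different primary analysis sets. The Blinding section says that the statistician analysing the data will not be blinded, so the choice is better fixed beforehand.

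**Working it through.** **Thresholds.** Half of 3 items is 1.5, so a 3-item subscale needs at least 2 answers and fails with 2 or more blanks. Half of 4 is 2, so the 4-item subscale fails with 3 or more blanks.

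**The plan's own figure.** Inputs from the Sample size section: "We estimated a total sample size of 276 participants, 92 in each group, using the ANOVA test for three groups", "considering an average effect size of 0.2 with a significance level of 0.05 and 80% power", and 10% loss. Read 0.2 as Cohen's f. Power is the probability that a noncentral F with 2 and N − 3 degrees of freedom and noncentrality f²N exceeds the central 5% critical value.
- 82 per group (N = 246): power 80.4%.
- 82 / 0.9 = 91.1, rounded up to 92 per group; 3 × 92 = 276. The stated size reproduces.
- 276 × 0.9 ≈ 248 men: power 80.7%. All 276: 85.0%.

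**Missingness.** The protocol gives no rate. Two assumed patterns show the range.

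*Pattern A: scattered blanks, each item blank independently with probability p.*
- 3-item subscale fails: f3 = 3p²(1 − p) + p³.
- 4-item subscale fails: f4 = 4p³(1 − p) + p⁴.
- Rule as written excludes 1 − (1 − f3)⁴(1 − f4). Score-by-score rule excludes f3 from the primary.

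| p | As written | Score by score |
|---|---|---|
| 1% | 0.1% | 0.03% |
| 2% | 0.5% | 0.1% |
| 5% | 2.9% | 0.7% |
| 10% | 11.1% | 2.8% |

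*Pattern B: a share q of men falls below half on each subscale, independently across the five.* The rule as written excludes 1 − (1 − q)⁵; score by score excludes q. The table starts from 276 men with no other loss.

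| q | Excluded as written | N, power | Excluded score by score | N, power |
|---|---|---|---|---|
| 1% | 4.9% | 262, 83.0% | 1% | 273, 84.6% |
| 2% | 9.6% | 249, 80.9% | 2% | 270, 84.1% |
| 3% | 14.1% | 237, 78.8% | 3% | 268, 83.9% |

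At q = 1%, (4.9 − 1) / 4.9 ≈ 80% of the men excluded would have a scorable primary outcome.

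If the full 10% loss also applied to the primary outcome, leaving 248 men, the written rule would leave 236 / 224 / 213 (power 78.6 / 76.3 / 74.0%) at q = 1 / 2 / 3%. The score-by-score rule would leave 246 / 243 / 241 (80.4 / 79.8 / 79.5%).

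*Correlated skipping.* If the same men fail all five subscales, both rules exclude q and the difference is zero.

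**The case against.** **The authors may have meant a rule for each score.** The sentence stands in the DCS scoring paragraph, between the calculation of partial and total scores and the scaling of the total. It can be read as leaving a subscale unscored when it is under half answered. That reading is reasonable and may be what was intended. But the sentence excludes participants, not scores, and from the analysis without qualification. The objection makes this a wording fault that is easily cured; it does not remove it.

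**The size rests on chosen inputs.** This stands. The five subscales belong to one questionnaire filled in at one session, and a man who stops or turns over a page would probably miss several together. Independence in pattern B is therefore unfavourable to the plan, and pattern A at 1–2% is negligible. The primary outcome is also collected in the same session as allocation, so little of the 10% allowance for men leaving the study should be used up by it. The figures that stack both losses are pessimistic.

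**Stronger readings that the protocol does not support.**
- A reader might infer a contradiction with "Participants will be analyzed in the group they were randomized to, regardless of actual intervention received". That sentence governs which group a man is counted in. It does not promise that every randomised man contributes an outcome.
- A reader might infer that the rule also removes men from the intention and 6-month screening analyses. The rule appears only in the DCS scoring paragraph, and nothing ties it to those outcomes. A clarifying clause is worth having, but this is not a stated defect.
- A reader might infer bias by arm, for instance because the explicit group has an extra task. That is possible but not shown. The Blinding section says that data collection is the same in every group.

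**Conclusion.** The point holds as a fault of wording with a real consequence. Followed literally, the rule discards observed primary outcomes because of blanks on items that the primary outcome does not use. The sample size itself is not in error.

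The loss cannot be stated as a fact. It runs from about 0.1–0.5% of men (scattered item blanks of 1–2%) to 4.9–14.1% (1–3% failing each subscale independently), against 1–3% under a score-by-score rule in the latter case. It approaches no difference if skipping is correlated. With no other loss, power stays above 80% at q = 1–2% and falls to 78.8% at q = 3%. The case for the change therefore rests less on power than on keeping valid primary data and fixing the analysis set unambiguously.

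**What to change.** Replace the rule with one applied score by score:
- **Primary:** a man is included if he answers at least 2 of the 3 values-clarity items. His score is the mean of the answered items rescaled to 0–100, whatever he left blank elsewhere.
- **Other subscales and the total DCS:** each follows its own stated completeness rule.
- **Intention and 6-month screening:** state that these analyses do not depend on DCS completeness.

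A multiple-imputation sensitivity analysis for men with fewer than 2 values-clarity items, using arm and baseline data, is optional. The cost is a sentence or two of analysis wording, with no new data and no change to the sample size. If a score-by-score rule was always intended, the edit only makes that explicit.

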### Data monitoring

Given the expected safety during the trial, no data monitoring committee will be established or interim analyses conducted.

### Protocol amendments

In the case of substantive protocol amendments an addendum will be submitted both to Ethics Committee and the Trial registry.

### Consent

After adequate explanation on the study procedures and aims by workgroup researchers and having the opportunity to discuss any questions or doubts with them, participants will fill in a written consent form, if they are willing to participate in the trial.

### Confidentiality

All the information related to the study will be stored securely at the study site. All participant information will be stored in locked file cabinets in areas with limited access at the University of Porto. All records containing identity elements, such as informed consent forms, will be stored elsewhere, separate from study records, and identifiable by a code number. All local databases will be secured with password. Any document with information that potentially links participant ID numbers to other identifying information will be stored in a separate, locked file in an area with limited access.

